## Abstract

**Background:**

The early identification of clinical deterioration in patients in hospital units can decrease mortality rates and improve other patient outcomes; yet, this remains a challenge in busy hospital settings. Artificial intelligence (AI), in the form of predictive models, is increasingly being explored for its potential to assist clinicians in predicting clinical deterioration.

**Objective:**

Using the Systems Engineering Initiative for Patient Safety (SEIPS) 2.0 model, this study aims to assess whether an AI-enabled work system improves clinical outcomes, describe how the clinical deterioration index (CDI) predictive model and associated work processes are implemented, and define the emergent properties of the AI-enabled work system that mediate the observed clinical outcomes.

**Methods:**

This study will use a mixed methods approach that is informed by the SEIPS 2.0 model to assess both processes and outcomes and focus on how physician-nurse clinical teams are affected by the presence of AI. The intervention will be implemented in hospital medicine units based on a modified stepped wedge design featuring three stages over 11 months—stage 0 represents a baseline period 10 months before the implementation of the intervention; stage 1 introduces the CDI predictions to physicians only and triggers a physician-driven workflow; and stage 2 introduces the CDI predictions to the multidisciplinary team, which includes physicians and nurses, and triggers a nurse-driven workflow. Quantitative data will be collected from the electronic health record for the clinical processes and outcomes. Interviews will be conducted with members of the multidisciplinary team to understand how the intervention changes the existing work system and processes. The SEIPS 2.0 model will provide an analytic framework for a mixed methods analysis.

**Results:**

A pilot period for the study began in December 2020, and the results are expected in mid-2022.

**Conclusions:**

This protocol paper proposes an approach to evaluation that recognizes the importance of assessing both processes and outcomes to understand how a multifaceted AI-enabled intervention affects the complex team-based work of identifying and managing clinical deterioration.

**International Registered Report Identifier (IRRID):**

PRR1-10.2196/27532

## Introduction

### Background

The timely identification of hospitalized patients who are clinically deteriorating is critical for facilitating prompt clinical interventions to improve patient outcomes but remains challenging for hospital systems to perform consistently. Artificial intelligence (AI), in the form of statistical models that predict clinical deterioration, is increasingly being considered by hospitals to aid in the early identification of these patients. Many such prediction models have been developed and reported in the literature, ranging from the sequential organ failure assessment score, which predicts inpatient mortality [1], to more recently developed machine learning models that predict a variety of outcomes, such as transfer to the intensive care unit (ICU), codes, and rapid response team (RRT) events [2-5]. However, few instances of these models have been shown to improve patient care, and there is little insight into how to implement interventions that use machine learning prediction models in the real-world setting [6]. A recently reported multisite prospective study of an intervention that used a model to predict inpatient clinical deterioration demonstrated improved clinical outcomes such as mortality rate and ICU length of stay in the intervention cohort, but there were no observed differences in the process measures, and it remains unclear which features of the implementation mediated the observed clinical benefit [7]. Therefore, although this particular intervention did demonstrate a clinical benefit at the participating study sites, there remains a pressing need for a deeper understanding of *how* such interventions can be effectively designed and implemented using AI to successfully disseminate them across other health care systems. As AI prediction capabilities in health care continue to grow, this implementation gap must be addressed to successfully leverage these capabilities to improve health care delivery.

One key question to address to close this implementation gap is how AI predictions can mediate changes within a complex work system to improve outcomes. Using a systems engineering lens, health care delivery—for example, for patients who are clinically deteriorating—can be viewed as occurring over a set of interconnected units (ie, people, technologies, and physical objects) that form distinct structures, processes, and patterns of behavior that lead to outcomes [8,9]. These health care work systems are typically considered to be *complex*, where the individual units dynamically interact with each other, self-organize, and adapt to the environment to form collective emergent properties that are difficult to predict and usually observed only after the system is live in the real world [10]. These systems are also described as *sociotechnical* because of the ways in which people and organizations (eg, patients and health care providers) interact with technology to make decisions, complete tasks, and form relationships and other organizational structures [11]. Emergent properties such as new workflows and habits, communication patterns, team structures, and cultures that arise from the introduction of new technologies may lead to unanticipated outcomes, barriers, or facilitators to the implementation of these technologies. In a systems thinking framework, the AI prediction model is not thought of as a standalone intervention but rather as an enabling component of a complex work system that mediates change [6].

Efforts to implement new technologies such as AI in health care often fail to consider the complexity of the sociotechnical systems in which these technologies are required to operate and underappreciate the unanticipated system-level effects that the technology may have on the health care delivery environment, and these effects can affect the success of the implementation [12]. For example, existing implementations of clinical deterioration prediction models typically assume a linear causal chain between the generation of an alert from the prediction model and the downstream actions of the receiving clinician who mediates the change in the outcome. However, they often do not explicitly consider and evaluate system-level properties such as the communication patterns and relationships among different members of the clinical team (eg, physicians and nurses), the degree to which the team members accurately share a mental model of risk, and the workflows and habits that evolve from the introduction of the AI prediction model. Evaluations of these implementations are therefore limited to only assessments of the clinical outcomes and select process metrics, and they do not capture the emergent properties that may help explain the barriers and facilitators to implementation and how the intervention mediates the changes in outcomes.

### Objectives

This paper presents a theory-driven study protocol informed by systems thinking and implementation science to assess the clinical and implementation outcomes of an implementation of a sociotechnical work system enabled by an AI prediction model for the early identification of hospitalized patients at risk of clinical deterioration. This protocol has three aims to (1) assess whether the AI-enabled work system improves clinical outcomes, (2) describe how the clinical deterioration predictive model and associated work processes are implemented, and (3) define the emergent properties of the AI-enabled work system that mediate the observed clinical outcomes.

## Methods

### Theoretical Framework

The Systems Engineering Initiative for Patient Safety (SEIPS) 2.0 model will be used as an analytic framework for this study [13]. The SEIPS model takes a person-centered approach to understand work processes within a sociotechnical system that is well suited to studying the impact of a technical solution (predictive model in the electronic health record [EHR]) on human work processes (management of hospitalized patients). The SEIPS framework characterizes outcomes as a product of a work system made up of factors related to the internal and external environment, people, organization, tools and technology, tasks, and work processes [8]. The revised model (SEIPS 2.0) incorporates the concepts of configuration, engagement, and adaptation, which better reflect a more dynamic implementation process among people, their environments, and the outcomes they produce [13].

### Setting

The intervention will be implemented in 6 primary general medicine adjustable acuity units at a quaternary academic hospital in the United States. The hospital has 605 beds, and most general medicine patients are cared for in 6 primary general medicine units. Each unit is served by physician teams, each with an average census of 12 and a maximum census of 20. The physicians spend most of their day rounding in many units and access the EHR through mobile devices, whereas the nurses spend most of their day in 1 unit working on a mobile desktop computer. These work setting characteristics were a key consideration in the intervention, implementation strategy, and study design.

### Intervention Description and Model Validation

The intervention is conceptualized as a work system comprising the following three parts: an AI model that predicts clinical deterioration, a mechanism for delivering the model predictions to clinical teams, and a multidisciplinary workflow driven by physicians and nurses. The clinical deterioration prediction model, the clinical deterioration index (CDI), was developed by Epic Systems Corporation and built into its EHR platform. The CDI is a logistic regression that runs every 15 minutes for all hospitalized patients using the most recent available clinical data of 31 physiological measures captured in the EHR and generates a score between 0 and 100, with higher scores indicating an increased risk of clinical deterioration as defined by any one of the following: ICU transfer, inpatient code, RRT event, or death. Between January 2020 and May 2020, the model was prospectively validated on 6232 hospital encounters of patients admitted to the implementation site for its accuracy in predicting ICU transfer or RRT event within 6-18 hours of the prediction, which was deemed by the clinical stakeholders to be an appropriate time interval that would allow for a meaningful clinical response. Of these 6232 encounters, 152 (2.44%) were unplanned ICU transfers and RRT events. The area under the curve was 0.70, and a model score threshold of 65 (out of 100) was chosen to maximize the positive predictive value and sensitivity of 0.20. Of note, this validation strategy was an enhancement of the vendor’s validation, which reported model accuracy in predicting the outcomes *without* the 6-hour to 18-hour time lag; this was thought to not be clinically meaningful because a model predicting an event to occur within the next 6 hours would not provide sufficient time for a clinical response to be effective.

Participatory design sessions using design thinking and process improvement methods were conducted with clinicians, including physicians, residents, and nurses. The participating clinicians generally preferred to be alerted only when patients were identified by the model as *high risk* rather than see the model prediction for every patient. Therefore, we designed the system to only flag patients whose CDI score was higher than 65, which, based on our validation, was the optimal cutoff to identify patients at the highest risk for unplanned ICU transfers and RRT events. As the area under the curve was only 0.70, the discriminatory ability of the model was not sufficiently robust to warrant showing the individual integer score values (ie, we did not want users to mistakenly interpret a higher integer score within the high-risk group as translating into higher risk) [2,4]. Rather, we incorporated a population-level description of patients in the high-risk group with the statement that the flagged patients have a *1 in 5 chance of requiring a RRT or ICU transfer within the next 6-18 hours,* which is derived from our validation.

Three preferred alerting mechanisms for a patient identified by the model as high risk were identified: alert mode 1: a noninterruptive flag icon that appears on the screen next to patients classified as high risk in the EHR patient list view, which allows clinicians to quickly see the names of all patients classified as high risk on one screen; alert mode 2: a banner visible on top of the screen once the chart of a flagged patient is opened that provides additional information about what *high risk* means, the accuracy of the CDI model, and specific next steps that should be taken to assess the risk of deterioration; and alert mode 3: an interruptive alert delivered to mobile devices that includes the same information as the banner at the time a patient first crosses the high-risk CDI threshold.

Downstream workflows were designed to accompany these alert modes to improve the reliability and degree of team coordination in the clinical response for patients at risk of deterioration (Figure 1). Once the clinician receives the alert, they first assess the patient to judge whether the alert is clinically relevant and accurate and then conduct a huddle with the rest of the clinical team and use the following checklist to assess the patient’s risk and review mitigation strategies:

Align on the anticipated reason for patient deterioration.Assess vital signs, airway or oxygenation needs, intravenous access, and code status.Agree on changes to care management (eg, aspiration precautions in place, critical care consultation, etc).Agree on the steps to take if the patient continues to deteriorate.

The last step involves documentation using an EHR-based documentation tool that captures the actions to be taken and the decisions made during this risk-of-deterioration huddle.

**Figure 1 figure1:**
[figure not shown]
Workflow for assessing and managing clinical deterioration following an alert from the Clinical Deterioration Index prediction model. EHR: electronic health record.

### Implementation Strategy

The intervention implementation will be split into two stages to assess its impact when offered to the physicians only (stage 1) and later to the entire physician-nurse team (stage 2). In stage 1 (yellow shading in Figure 2), the three alert modes will be delivered only to the physicians for patients across all 6 patient care units, and subsequent workflows will be initiated only by the physician.

In stage 2 (green shading in Figure 2), the alert modes will also be delivered to the nurses on the clinical teams, and either the physician or the nurse on the team can initiate the downstream workflow, thus creating a team approach to identifying and managing clinical deterioration. Nurses are to perform a parallel clinical validation of the alert and contact the physician to conduct the aforementioned risk-of-deterioration huddle. Thus, assessment of the risk and initial steps to manage deterioration can be initiated by either the physician or the nurses in the team intervention model. Stage 2 will be rolled out in a stepwise manner to each of the 6 primary general medicine units.

Rolling out the intervention using a stepwise approach was chosen for pragmatic implementation and evaluation purposes. The physicians care for patients across all 6 patient care units, whereas the nurses are staffed based on individual units. For implementation practicality and patient safety, stage 1 (physician-only intervention) would thus be implemented across all 6 units, whereas the implementation of stage 2 (the addition of nurses) would be staggered by the patient care unit so that the nurses in each unit can be trained in the new workflow together. This implementation strategy also allows us to evaluate the additive impact of delivering AI predictions to the entire physician-nurse team using a stepped wedge design.

**Figure 2 figure2:**
[figure not shown]
Stepped wedge design for the implementation and evaluation of a clinical deterioration model and workflow. Under *Baseline* column, blue shading includes data from the 10 months prior to the roll-out of the intervention for all 6 participating units (60-unit months for analysis). Under *Month* column, yellow shading represents stage 1 and the physician-only intervention for the physician-nurse team (25-unit months for analysis). Under *Month* column, green shading indicates stage 2 and the intervention for the physician-nurse team (41-unit months for analysis).

### Study Design

To evaluate this complex, multicomponent intervention, we will use a mixed methods approach informed by the SEIPS 2.0 model to achieve our aims of assessing both the clinical outcomes and the processes that produced these outcomes. We found this model to be uniquely equipped to assess the impact of a new technology such as a predictive model because it takes into account both the social and technical aspects of implementation. Using a mixed methods approach will provide complementary data on the effect of the AI-enabled model on the management of clinical deterioration (ie, quantitative data will evaluate the clinical outcomes, and qualitative data will evaluate the processes) [14]. The intervention will be implemented consecutively in the medicine units based on a modified stepped wedge design featuring three stages (Figure 2): the baseline period (stage 0, blue shading) includes the 10-month period before the implementation of the intervention; in stage 1 (yellow shading), the intervention will be launched to all general medicine physicians across the hospital; and in the third and final phase (green shading), the intervention will be launched to the full physician-nurse clinical team in a staggered approach by medical unit. The study began in March 2021 (month 1).

### Sample

To evaluate this multidisciplinary intervention, data derived from multiple stakeholders, including providers, staff, and adult patients, will be included. The intervention will be implemented by providers and clinical staff in the 6 medicine units for all adult patients, as outlined in Figure 2. The clinical and process outcomes derived from the EHR and chart reviews will be captured at either the patient or unit level. The following patient inclusion criteria are based on the level of analysis:

For unit-level outcomes, all patients admitted to the units will be included in the analyses.For patient-level outcomes, patients who cross the high-risk CDI threshold (CDI≥65) during their inpatient stay and will thus be eligible for the intervention will be included in the analyses.

For the qualitative evaluation, a stratified purposeful sample of approximately 20 providers and clinical staff who are typically responsible for identifying deterioration in patients will be selected for interviews (eg, hospital residents or interns, bedside nurses, critical care response team, clinical nurse specialists, and ICU fellows) [15].

### Outcomes

The clinical outcomes will be derived from data extracted from the patients’ EHRs related to inpatient hospital stay and up to 30 days after discharge to capture readmission. Using these data, the outcomes will be calculated and expressed at either the unit or patient level, as described herein. To facilitate generalizability and comparisons with other outcomes, the following outcomes, which are commonly assessed in other interventions for clinical deterioration [2,5,16], will be evaluated to address aim 1:

Number of RRT activations in response to adverse events per unit per month (RRT/unit/month; unit level)Number of code events per unit per month (codes/unit/month; unit level)Number of ICU escalations per unit per month (ICU/unit/month; unit level)Mortality per unit per month (deaths/unit/month; unit level)Readmission rates (30-day rates) per unit per month (30-day readmissions/unit/month; unit level)Length of stay in acute inpatient setting (patient level nested in unit)

We will also explore the process outcomes informed by the SEIPS 2.0 model and the implementation outcomes described by Proctor et al [17] to assess the ways in which the model and workflow changed the work system and, subsequently, the work processes (aims 2 and 3). Where possible, these outcomes will be derived from the patients’ EHRs and a secure text messaging platform to minimize the required data reporting by clinicians. A focused chart review of a subsample of patients will also be conducted for data not extracted through the methods described previously. Examples of these processes include the following:

Completion of documentation in the EHR (unit/month; unit level)Number and type of staff engaged in the intervention workflow (patient level nested in unit)Actions taken by the team engaged in the intervention workflow (patient level nested in unit)Time elapsed between alert and completion of workflow procedures, including documentation (patient level nested in unit)

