### Analysis

#### Quantitative Analysis

The primary aim is to assess the impact of the physician-only and team interventions on the unit-level clinical outcomes compared with baseline data. The secondary aim is to explore how the intervention is implemented by describing the process outcomes that were developed and launched as part of the intervention-specific workflow. For these process outcomes, the differences between the physician-only and team interventions will be statistically evaluated because baseline data will not be available for these outcomes. Poisson regression will be applied for unit-level count outcomes to determine the differences among the three phases of the study (baseline, physician-only, and team), followed by pairwise comparison. A multilevel, mixed-effects model will be used for patient-level outcomes to include the covariate unit to account for nesting. The level of statistical significance will be set at *P*<.05.

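### The five unit-level clinical outcomes are fixed per unit-month with no stated patient-volume denominator, so any difference in volume between phases would enter the rate ratio one for one

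*Protocol article*

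**What the plan says.** The Outcomes section lists six clinical outcomes for aim 1. Five are unit-level: RRT activations, code events, ICU escalations, deaths and 30-day readmissions. Each has the unit-month as its unit. The first is "Number of RRT activations in response to adverse events per unit per month (RRT/unit/month; unit level" and the fourth is "Mortality per unit per month (deaths/unit/month; unit level". The readmission outcome reads "Readmission rates (30-day rates) per unit per month (30-day readmissions/unit/month; unit level", so it is named a rate but carries the unit of a count. The sixth outcome, length of stay, is at patient level and is not affected by this point.

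The Sample section says who contributes: "For unit-level outcomes, all patients admitted to the units will be included in the analyses". The Quantitative Analysis section gives the model, "Poisson regression will be applied for unit-level count outcomes to determine the differences among the three phases of the study (baseline, physician-only, and team", and the comparator: "The primary aim is to assess the impact of the physician-only and team interventions on the unit-level clinical outcomes compared with baseline data". The Power Calculation section uses the percentage reduction in RRT per unit-month as its effect measure, with 60 baseline and 41 team unit-months as exposure. The caption of Figure 2 counts the data for analysis in unit-months too.

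Patient-days, admissions and discharges are not named as a denominator, offset or covariate in any of these sections.

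**The concern.** A unit-month is a fixed amount of calendar time, not a fixed number of patients at risk. The unit-level outcomes cover everyone admitted, so the expected count is risk per patient multiplied by patient volume. A Poisson comparison of counts per unit-month estimates the change in that product.

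Two features of the design make this matter for the primary contrasts. Baseline "includes the 10-month period before the implementation of the intervention" and the intervention months follow it, so the two cover different calendar time. Also, under Implementation Strategy, all 6 units enter the physician-only stage together, so no concurrent baseline unit would share a shift in volume. The contrast of team with physician-only has some concurrent units and is less exposed.

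For readmissions, the patients at risk are those discharged alive. If more patients are discharged, readmissions per unit-month rise even when the risk per discharge is unchanged.

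At stake is the reading of all five outcomes. A quieter intervention period would look like benefit. A busier one would hide a real benefit or look like harm.

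**Working it through.** **Inputs from the Power Calculation section, scenario 1:** 4.5 RRT per unit-month in every unit; 60 baseline and 41 team unit-months; two-sided alpha 0.05.

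**Assumed input:** d, the relative change in patient volume in team months against baseline. The article gives no figure for it. Its only census figures are per physician team (average 12, maximum 20), not per unit or phase.

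**Expected counts with no effect and no shift:** baseline 4.5 × 60 = 270; team 4.5 × 41 = 184.5.

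**Test:** Wald test on the log rate ratio with unit-months as exposure. If the true ratio per patient is R, the ratio per unit-month is RR = R × (1 + d). Then SE = √(1/270 + 1/(184.5 × RR)), and rejection occurs when |log(estimated RR)|/SE exceeds 1.96.

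**Step 1, the article's own figure.** R = 0.75, d = 0: SE = √(1/270 + 1/138.4) = 0.1045; |log 0.75|/SE = 0.2877/0.1045 = 2.75; power = Φ(2.75 − 1.96) = 78.6%. Simulations of 10,000 trials gave 79% to 81%. This agrees with the stated 80% power at approximately 25%, so the power basis is reproduced with unit-months as the only exposure.

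**Step 2, no true effect per patient (R = 1).**

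| Assumed volume change d | RR per unit-month | False rejections |
|---|---|---|
| 0% | 1.00 | 5.0% |
| −2% | 0.98 | 5.5% |
| −3% | 0.97 | 6.2% |
| −5% | 0.95 | 8.3% |
| −10% | 0.90 | 18.8% |
| −15% | 0.85 | 36.7% |

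For falls of 5% or more, nearly all rejections point to benefit. For d = −10%: SE = √(1/270 + 1/166.05) = 0.0986; log(0.90)/SE = −1.07; Φ(−1.96 + 1.07) ≈ 18.6% towards benefit, plus about 0.1% towards harm. Rises of 5% and 10% gave 8% and 18% in simulation, nearly all as apparent harm.

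**Step 3, a true 25% reduction (R = 0.75).**

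| Assumed volume change d | RR per unit-month | Power |
|---|---|---|
| 0% | 0.750 | 78.6% |
| +5% | 0.7875 | 64.1% |
| +10% | 0.825 | 47.5% |

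**Step 4, the same model with a log(exposure) offset.** In simulations of 40,000 trials, false rejections stayed between 4.8% and 5.1% for every volume change from −25% to +20%. With a true 25% reduction and volume up 10%, power was 82%.

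Scenarios 2 and 3 depend on the step pattern in Figure 2, which is not shown here. They were neither confirmed nor refuted, and the point does not need them.

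**The case against.** The strongest objection is that the missing offset is partly read from silence. The analysis section says only that "Poisson regression will be applied for unit-level count outcomes" and lists no model terms at all; an article commonly leaves offsets and covariates to the fuller plan. A reader might infer that the trial will certainly be analysed without an exposure term. The article does not establish that. What it does state is the unit-month as the unit of all five outcomes and as the only exposure in the power calculation. Those are choices, not omissions. A later offset would change the quantity that the article defines and powers.

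Second, the bias is conditional. A reader might infer that the result will be biased, but no section shows that volume differs between phases, and a shift of 2% to 3% does little harm. This stands, and the figures above must be read as a range over assumptions.

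Third, an offset is not free of drawbacks. Patient-days equal admissions times length of stay, and length of stay is itself an aim-1 outcome. If the intervention shortens stays while events per admission stay the same, the rate per patient-day rises. ICU escalation also removes patient-days from the unit. This stands too, and it decides which denominator should lead.

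Fourth, the readmission label could be shorthand for a proportion tabulated by month. That is possible, but the name and the unit still disagree within one line.

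**Conclusion.** The point holds in conditional form. Outcome definition, model and power basis all rest on the unit-month, and no patient-volume denominator is stated. Followed as written, the analysis would carry any volume difference into the rate ratio in full, in either direction, and the contrasts with baseline have no concurrent units to reveal or absorb it. The size depends on the shift: slight at 2% to 3%, material from about 5%, and serious at 10% to 15%. These figures rest on scenario 1 rates, Poisson variation and a uniform volume shift across units. The readmission outcome needs correcting whether or not volume shifts, because its name and unit conflict.

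This is a change that should be made. It is not proof that the trial's result will be wrong. A reader might also infer that an offset would make the baseline contrast sound. It would not: it removes the volume component only and leaves secular trend and case mix untouched.

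**What to change.** In Outcomes and Quantitative Analysis:

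- For RRT activations, codes, ICU escalations and deaths, add a log-exposure offset to the Poisson models. Use admissions (or patients at risk) in the unit-month as the main denominator, and repeat with patient-days as a sensitivity analysis.
- Define 30-day readmissions per live discharge, analysed with log(live discharges) as the offset or with a binomial model.
- Fix the choice of denominator before the outcome data are compared, and give the reason: patient-days may themselves respond to the intervention through length of stay.
- Keep the raw counts per unit-month as a descriptive measure of workload.
- In Power Calculation, restate the effect on the new scale, or say that volume is assumed equal across phases.

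The cost is small. The EHR extraction already planned should supply admissions, patient-days and live discharges by unit and month, and the model gains one term. The drawback is that the main denominator becomes a deliberate choice of what is being estimated, and results per admission and per patient-day may differ if length of stay changes. Reporting both makes that visible.
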